## Abstract

**Background:**

The current standard of interpretation provision is not efficacious or not acceptable to Deaf patients who communicate using sign language. In-person or video relay interpretation (VRI) sign language interpretation is largely unavailable. There are no clear data on the availability of VRI or in-person interpretation. Given the limited number of available sign language interpreters and the cost, VRI may be more available than in-person. Existing evidence tends to focus on assessing personal preferences of Deaf users regarding interpretation and interpreters’ preferences. Although respecting preferences is essential, there is a vacuum of knowledge on how the format of access to interpretation impacts the quality of communication between Deaf persons and health personnel.

**Objective:**

This study aims to look at the effectiveness of the VRI system in improving communication outcomes between Deaf patients and doctors versus the available standard of care of the usual communication tools, including informal interpretation, lip- or note-reading, and using their mobile phones to contact a formal or informal interpreter, for Deaf patients aged 18 years and older in Bogota, Colombia.

**Methods:**

This is a randomized controlled trial with a total sample size of 216 participants, divided into 2 groups: an intervention group, which receives a medical appointment using VRI, and a control group, which receives a medical appointment using standard communication. Both the Deaf participants and the health care professionals will be blinded to the allocation, as they will not know whether the appointment will involve VRI or standard communication until they arrive at the office. The primary outcome measure will be an assessment of communication using a Doctor-Patient Communication Scale. This scale was translated into Colombian Sign Language following a rigorous cultural adaptation and translation procedure. Furthermore, the database contains key clinical variables and recommendations provided by the doctor during a general medicine appointment. We will compute associations.

**Results:**

Recruitment opened on August 24, 2023. As of July 2024, 180 participants had been enrolled. The intervention and data collection were finalized in October 2024. The findings of this study are expected to be submitted for publication in early 2025.

**Conclusions:**

This study will provide rigorous evidence regarding information and communications technology intervention in health care, addressing empirical challenges in using inclusive research designs in public health. In addition, effective VRI models that address the challenges faced by Deaf people will be tested, implemented, and maintained in low- and middle-income countries. A disability-inclusive evaluative tool for quality communication mediated by VRI in health care is also tested. Ultimately, this will lead to evidence-based recommendations for implementing the Convention on the Rights of Persons with Disabilities (CRPD) in mobile health contexts.

**Trial Registration:**

ClinicalTrials.gov NCT05966623; https://clinicaltrials.gov/study/NCT05966623

**International Registered Report Identifier (IRRID):**

DERR1-10.2196/64590

## Introduction

Sign language interpretation is essential for facilitating communication between Deaf people and hearing individuals; it creates a cultural and linguistic bridge. There is growing evidence showing that communication barriers between health care staff members and Deaf patients are the main factors for health disparities. Deaf people continue to experience a lack of access to health care services in their preferred language; there is insufficient health information in sign language and insufficient knowledge and awareness by professionals of their linguistic and cultural requirements [1,2].

The current standard of interpretation provision is not efficacious or not acceptable to Deaf patients who communicate using sign language. In-person or video relay interpretation (VRI) is largely unavailable. There are no clear data on the availability of VRI or in-person interpretation. Given the limited number of available sign language interpreters and the cost, VRI may be more available than in-person interpretation. Existing evidence tends to focus on assessing personal preferences of Deaf users in regard to interpretation and interpreters’ preferences. Thus, there is a vacuum of knowledge regarding whether this format of interpretation succeeds at enabling quality communication, which is core to the purpose of interpretation services. A handful of studies, all from high-income countries (HICs), predominantly the United States, provide some empirical data comparing VRI in-person interpretation [3] and show no statistical difference in their preference for VRI versus in-person interpretation for critical care, but a statistical difference for noncritical care. Myers et al [4] reported that their study participants preferred in-person interpreting due to recurrent technical difficulties with VRI. Kushalnagar et al [5] found that most people in the United States do not have access to VRI, but those with access stated that such access would meet their interpretation needs as much as in-person does [5]. Hall and Ballard [6], using a qualitative exploration of preferences, claim that Deaf people are inclined to prefer in-person interpretation, while noting that such provision is highly constrained due to shortages in the workforce. Assessing the efficiency of VRI versus the standard of care would be of more value, given that there is no other effective intervention to compare.

### Access to Health Care for Deaf People

Access to health care services for Deaf people has historically been poor compared with the hearing population. Deaf people have worse mental and physical health than the hearing population [1,7]. Deaf people are at high risk of developing cardiovascular diseases, diabetes, depression, overweight, and obesity; they also have a higher risk of partner violence and depression, and there is a higher suicide rate [8,9]. They are more prompt to underdiagnosis, and undertreatment of chronic diseases can put them at risk of preventable diseases and potentially reduce their life expectancy [9]. Furthermore, those in low- and middle-income countries (LMICs) are exposed to higher health disparities than those living in HICs [10,11].

### Challenges to the Provision of Sign Language Interpretation

Deaf people are more likely to avoid health care providers, partially because of the lack of means of communication with these providers and available interpreters [12,13]. Thus, even if interpreters are available, the pool of sign language interpreters tends to be relatively small, even in HICs [14]. Shortages are more acute in LMICs, where official certification is often unavailable or limited. For example, in 2015, there were approximately 42 certified sign language interpreters in Mexico [15] and 37 certified interpreters in Paraguay [16]. Sign language interpretation is often a service delivered by people who have completed a certain number of hours in sign language courses and who subsequently present themselves in institutions offering their interpreting services without an official degree and without specific studies that train them in the educational field [17]. The vacuum of available workforce and training is an issue in HICs, too. Deaf people associations in Spain and Canada have called for attention to this issue [18,19]. Furthermore, aside from the availability, the competencies of those interpreting in the health care context are a concern, as specific health communication training is mainly absent [11,20,21]. Significant progress has been made by other countries, like the United States and England, which have stabilized frameworks and regulations and standardized training systems quality standards [22].

Aside from issues of availability and competencies of the sign language interpretation workforce, a second barrier to the interpretation process is the lack of skills in health personnel. Health personnel at large tend to be unaware and unskilled in working with sign language interpreters, which, alongside limited awareness about deafness overall, often results in poor communication and, ultimately, patients not getting the information they need to decide on their health or treatments [14]. Good communication between health personnel is critical to patient experience and quality of care [23]. Furthermore, good communication has positively improved patient health outcomes [24].

One solution to these limitations is the growing availability of VRI, a specialized translation service that relies on a high-speed internet connection and a camera to connect a remote sign language interpreter with a health care professional and a Deaf patient to facilitate their communication [5]. VRI technology is not subject to geographical or time limitations, as the interpreter can provide their services from anywhere without having to travel to the appointment. As sign language interpreters are mainly unavailable due to workforce constraints, building capacities in this sector will take many years or generations, especially in LMICs. Therefore, VRI can be a good solution for enabling communication between health care staff members and Deaf people.

### Trial Objectives and Purpose

Available data tend to focus on the evaluation of the personal preferences of Deaf users regarding interpretation, as well as the preferences of interpreters. This is useful, but knowing whether these preferences translate into better communication and health services relationships and outcomes is unknown. Furthermore, assessing the feasibility of in-person services, scalability, and sustainability are often left behind. Hall and Ballard [6] show that Deaf people prefer on-site interpretation, acknowledging the workforce shortage and operational challenges in the short term in the United States [6]. From a different angle, in Colombia, [name] et al (unpublished data, 2024) documented that in tight-knit Deaf communities, some people prefer VRI, reporting a greater feeling of privacy in health-related settings. As evidence grows, and the interpretation workforce may also increase and mature in their competencies and regulation, it is pertinent to ask if VRI technology could enable health systems to make the most of the available workforce and enable Deaf communities to communicate effectively with health personnel. There are no baseline data on this issue nor evidence of the effectiveness of the technology compared with the standard of care, which includes informal interpretation, lip-reading or note-taking, or using their mobile phones to contact a formal or informal interpreter. A total of 80% of Deaf people live in LMICs; therefore, running a study in such a setting shall have more global implications.

This study is being conducted in Colombia. The following criteria were used to select this country: (1) it is a signatory country to the Convention on the Rights of Persons with Disabilities (CPRD); (2) it has demonstrated legislation, commitment, and progress of being a champion for inclusive information and communications technology (ICT; G3ICT and Zero Project International Telecommunication Union); (3) it has the necessary infrastructure to test a working model for VRI in the health care context, which includes good internet coverage throughout the country, availability of VRI for general use, and a workforce of local sign language interpreters with expertise in VRI; (4) is a high- to middle-income country, and variations within its territory are relevant for both LMICs and HICs; and (5) Deaf peoples’ organizations have interest in this study and have infrastructure that could support both the survey and the intervention. The researchers are working in partnership with local and international disabled people organizations. The Ministry of Health and Universidad del Rosario are the implementing partners.

## Methods

### Design Based Upon the Real-Life Context in Colombia

This study trial is part of a larger study that focuses on understanding structural and societal factors alongside impairments to determine how an individual experiences health and disability (Swiss National Science Foundation, PZ00P1_186035). A steering committee governs the design of the study. The committee includes local and international Deaf organizations, leading disability and global health scholars, and public administration representatives.

A nuanced understanding of disability, which considers lived experiences, cultural differences, and intersectionality issues, is essential to inform research on the effectiveness of public health interventions. For instance, examining whether Deaf people and health providers could enable access to VRI and, therefore, mobile devices with video capabilities and the internet requires analysis at multiple levels. In the first part of the study, we ran a health priority assessment through a national e-survey in Colombian Sign Language. This survey rigorously linguistically and culturally adapted research instrument design to measure key indicators and health priorities of the Deaf community and contribute to understanding health inequities by using population comparison. Then, using qualitative interviews, the team looked at the individual-level determinant factors such as technology literacy, device adequacy, affordability, and availability. Then, we collected data on infrastructure, workforce, and health policies in tandem with interviews with health workers and sign language interpreters. This first part revealed where and how exclusion occurs within and outside the health system. Understanding their specific health care needs is paramount. This exploration enables us to determine the most effective model for such interventions, and taking action to improve VRI use across health care systems is a critical step. The design intervention addressed was developed to provide sign language with a fully qualified sign language interpreter, although formal training on health is not available in the country and region. Significant expertise in the health sector was a prerequisite to act as an interpreter in the study. Accessibility issues from the first point of contact with the health setting were considered. The design of the VRI randomized control trial (RCT) study responded to real-life contexts in Colombia.

### Participants in the Sample

This study is an RCT with a total sample size of 216 participants, divided into 2 groups: an intervention group, which receives a medical appointment using VRI, and a control group, which receives a medical appointment using the standard communication (informal interpretation, lip-reading, note-taking, or the use of mobile phones). Both the Deaf participants and the health care professionals will be blinded to the allocation, as they will not know whether the appointment will involve VRI or standard communication until they arrive at the office.

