### Intervention Group

The participants were able to learn about the study through social media, advocacy organizations, and word-of-mouth. A researcher, along with a sign language interpreter, contacts each potential participant through a WhatsApp video call (the key communication channel among Deaf organizations in Colombia, using sign language) to explain the project and schedule a medical appointment. Upon arrival at the hospital, participants are greeted by a research assistant who facilitates their admission process. The participants were then guided to the consultation room.

The participants engage in a standard medical consultation known in the Colombian health system as “standard promotion and disease prevention or annual check” using VRI as the means of communication. During the consultations, the health care professional conducts a medical history assessment, performs a physical examination, and provides education and recommendations based on the findings.

The VRI is used during the appointment. A 32-inch screen displays the Colombian Sign Language interpreter, who connects through the Zoom (Zoom Video Communications) platform. A professionally accredited Colombian Sign Language interpreter with robust experience in medical interpretation facilitates communication between the health care professional and the Deaf participant during the consultation.

After the medical consultation, participants complete the Doctor-Patient Communication (DPC) scale. This scale is administered by a research assistant using a tablet and is available on the LimeSurvey platform with Spanish subtitles and Colombian Sign Language videos.

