### Assignment of Interventions: Blinding

To prevent selection bias, the participants will be assigned to the intervention or control group using random assignment techniques with block randomization. The randomization of participants will allow for the evaluation of treatment effects while ensuring that the observed outcomes are truly due to the treatment and not influenced by other factors. Using blocks in random assignment is a common strategy to ensure that the groups are balanced in terms of relevant characteristics, which helps minimize variability and potential biases in assigning patients to the study groups. In this case, a randomization list will be created using the website randomization.com. This site will facilitate random assignments using the block method to ensure a balanced allocation of patients between the 2 groups.

A defined procedure will be followed to define the block randomization lists.

First, determining the block size: a block size of 4 will be defined (2 patients for each group). This block size is chosen because it is a multiple of the number of groups, which in this case are 2 (intervention and control). Having a block size that is a multiple of the number of groups ensures that each group is equally represented within the blocks, which aids in maintaining a balanced random assignment of patients to the intervention and control groups. This helps ensure the validity and reliability of the study results.

Second, randomly assigning each participant within a block to a group: for example, with a block size of 4 and 2 groups (control and intervention, A and B), the assignment could be as follows:

Block 1: ABBABlock 2: BAABBlock 3: ABABBlock 4: BABA

This process continues until all participants have been assigned to the different groups. To maintain concealment, the block sizes will not be revealed.

Once the participants enter the medical appointment, they will receive a box containing several envelopes. Each participant will select an envelope that will provide their participant code and the corresponding group designation (control or intervention). The researcher, the participant, the general practitioner, and the sign language interpreter will only learn the group to which the participant belongs when the envelope is opened upon entering the medical consultation.

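### The protocol calls participants and doctors blinded, but both learn the arm before the consultation that the participant then rates, and the limitations do not say so

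*Protocol article*

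**What the plan says.** The claim appears twice in the same words, in the Abstract (Methods) and in Methods, Participants in the Sample: "Both the Deaf participants and the health care professionals will be blinded to the allocation". The reason follows in the same sentence: "they will not know whether the appointment will involve VRI or standard communication until they arrive at the office".

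The allocation procedure stands under the heading "Assignment of Interventions: Blinding". There the participant picks an envelope at the appointment. Of the participant, the doctor, the interpreter and the researcher alike, the section says that they "will only learn the group to which the participant belongs when the envelope is opened upon entering the medical consultation". The same section says that randomization allows treatment effects to be evaluated while "ensuring that the observed outcomes are truly due to the treatment and not influenced by other factors".

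Under Intervention Group, the interpreter appears on a 32-inch screen in the consulting room. Under Control Group, the same consultation takes place without VRI. Under Primary Outcomes, the participant completes the DPC scale after leaving the consultation. Intervention Group adds: "This scale is administered by a research assistant using a tablet".

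**The concern.** Keeping the arm undisclosed until the consultation starts can protect the assignment from selection. It does not blind anyone during the consultation or when the outcome is rated. The protocol gives the first as its reason for claiming the second.

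This matters because the primary outcome is the participant's own judgement of how well the communication went. A participant who knows that the service under study was provided may rate generously, and one who knows that it was withheld may rate harshly. Neither effect can be separated from a real gain in communication. Someone relying on the Abstract would record participant and provider blinding for a trial that has neither, and would give a favourable DPC result more weight than it can bear.

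**Working it through.** **1. Sequence of events, from the protocol's own sections.**

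| Step | Who knows the arm | Section |
|---|---|---|
| Recruitment, scheduling, arrival | Participant and doctor do not | Participants in the Sample |
| Envelope opened on entering the consultation | Participant, doctor, researcher, interpreter | Assignment of Interventions: Blinding |
| Consultation, with or without the interpreter on screen | The same people; the difference is visible | Intervention Group; Control Group |
| Participant completes the DPC scale | Participant knows; the assistant's status is not stated | Intervention Group; Primary Outcomes |

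The communication being rated, and the rating itself, both come after disclosure. No section describes anyone as blinded from that point on. Participants in the Sample puts disclosure at arrival at the office, and the allocation section puts it at entry to the consultation. Either moment precedes the communication that is rated, so this difference does not affect the point.

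**2. Limitations.** Strengths and Limitations names two limits: complex or critical-care consultations, and secondary impairments that restrict who can take part. It mentions neither unblinded conduct nor self-rating of the primary outcome.

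**3. The protocol's own sample size.** Inputs from Sample Size: Zα = 1.64, Zβ = 0.84, p1 = 0.85, p2 = 0.65, margin δ = 0.05, equal groups, 10% dropout.

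n = (Zα + Zβ)² × [p1(1 − p1) + p2(1 − p2)] / [(p1 − p2) − δ]²
= (2.48)² × (0.1275 + 0.2275) / (0.15)²
= 97.04 per arm.

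Total = 2 × 97 / 0.90 = 215.6, rounded up to 216. Both stated figures are reproduced. None of them depends on blinding.

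**4. Illustration of what unblinded rating could do.** The bias b is an assumption; the documents give no value. Suppose VRI adds nothing, so that the true rate is 0.65 in both arms, but knowing the arm raises favourable ratings in the VRI arm by b. With n = 97 per arm:

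SE = √{[(0.65 + b)(0.35 − b) + 0.65 × 0.35] / 97}

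Chance of meeting the 5-point-margin criterion = Φ[(b − 0.05)/SE − 1.64]

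Chance of significance against zero difference (one-sided 5%) = Φ[b/SE − 1.64]

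| Assumed b | SE | Margin criterion | Against zero difference |
|---|---|---|---|
| 0 | 0.0685 | 1% | 5% |
| 0.05 | 0.0672 | 5% | 19% |
| 0.10 | 0.0654 | 19% | 46% |
| 0.15 | 0.0632 | 48% | 77% |

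The calculation uses the protocol's rounded Zα of 1.64 and the normal approximation. It treats the primary outcome as one yes/no proportion, as the sample-size section does, although the DPC scale has 13 items.

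**The case against.** The strongest reply is that nothing is hidden. The sentence claiming blinding explains what it means, and the allocation section lists who learns the arm and when. Masking a visible interpreter is not feasible, and the patient's experience of communication is a legitimate thing to measure. On this view the defect is one word with the facts beside it. Much of this stands: an unblinded self-rating is not in itself a design error here, and neither randomization nor sample size has to change. It does not rescue the word, which names a protection the design does not have, in the Abstract as well as the Methods.

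Several stronger readings are tempting, and the documents do not support them:

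- *That the protocol says blinding keeps the outcome free of other influences.* The sentence on other factors has randomization as its subject. It is too broad, because randomization balances baseline factors and does not remove expectation effects, but it makes no claim about blinding.
- *That false-positive rates follow from a two-sided Fisher test.* At 97 per arm, with 65% in control, that test would reject in about 9%, 28% or 60% of trials for the same assumed biases. The Analyses section names Fisher for associations among clinical variables and does not assign it to the DPC comparison between arms. The stated superiority criterion gives lower figures, and at a 5-point bias essentially no excess over 5%.
- *That participants were drawn from advocacy channels and so inclined to favour VRI.* Recruitment also used social media and word-of-mouth.
- *That the assistant sees or shapes the answers.* The protocol says only that the assistant administers the scale by tablet.
- *That masked analysis is missing.* This is commonly left to a statistical analysis plan, which is not shown.

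**Conclusion.** The point holds as a misstatement with a missing limitation. The protocol claims blinding of participants and health professionals. Its own procedure shows that both know the arm before the rated communication begins, and that the unblinded participant supplies the primary outcome. An analysis plan that is not shown could not make the claim true.

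The documents do not show that the result is biased, or by how much. On the assumed range of 5 to 15 points, the chance of a false claim runs from about 5% to 48% under the margin criterion and from about 19% to 77% against zero difference. The upper figures come from a bias smaller than the planned 20-point effect, so the limitation is material to how a positive result is read. These figures rest on a 65% true rate in both arms, 97 analysed per arm, and bias in the VRI arm only.

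**What to change.** - In the Abstract and in Participants in the Sample, replace the blinding statement with: open-label; the arm is not disclosed to participant, doctor, researcher or interpreter until the envelope is opened at the consultation. This wording says when the arm is disclosed. It deliberately does not certify the adequacy of concealment, which is a separate matter given the fixed blocks of 4 and the choice from a box of envelopes.
- Retitle the allocation section so that it does not claim blinding.
- Limit that section's sentence on other factors to the balance of baseline factors by randomization.
- State in the limitations and the conclusions that the primary result is an unblinded patient-reported rating, so that expectation or disappointment effects cannot be separated from a true gain in communication.

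The cost is wording only, plus a less favourable description of the design; the sample size stays at 216. A change to how the scale is administered is not proposed. The Abstract says data collection was finalized in October 2024 (the Results section says it was expected to finish then), so such a change would probably come too late.
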